## Methods/design

2

### Study design

2.1

GEOMETRY is a prospective, non-randomized, cohort, single-center study to investigate the relationship between plaque eccentricity, plaque vulnerability, and the risk for MACE in order to validate plaque eccentricity as a new CCTA marker of coronary plaque vulnerability.

### Ethics

2.2

The study protocol was approved by the Ethics Committee for Scientific Research of the University of Medicine and Pharmacy of Tirgu Mures (certificate of approval: 352/13.12.2017) and the Ethics Committee for Scientific Research of the Cardio Med Medical Center (certificate of approval 27/12.02.2017). All study procedures comply with the Declaration of Helsinki of 1975, and all patients will sign an informed consent prior to enrollment in the study.

### Study population

2.3

GEOMETRY will be a non-randomized, observational, single-center study including patients with chest pain and pre-test probability of coronary artery disease between 15% and 85%, referred for CCTA (according to the recommendation of the guidelines of the European Society of Cardiology).^[10]^

Inclusion criteria:

Patients with suspected coronary artery disease (CAD) and pre-test probability of CAD between 15% and 85%, who undergo CCTA, and in whom CCTA will identify presence of at least 1 significant coronary plaque (producing a luminal narrowing of at least 50%).Ability to provide informed consent.Age over 18 years.

Exclusion criteria:

Patients with pre-test probability of CAD >85% or <15%.Electrocardiographic evidence of ST-segment elevation acute myocardial infarction.Presence of pre-existing CAD including prior myocardial infarction.History of coronary artery revascularization (by percutaneous coronary intervention, stent, or bypass graft surgery).Atrial fibrillation or other irregular rhythm.Unwillingness or incapacity to provide informed consent.Allergy to iodine contrast media.Inability to tolerate beta-blocker medication.Renal insufficiency (serum creatinine values higher than 1.5 mg/dL) or renal failure requiring dialysis.Pregnant women or lactation.Active malignancy or malignancy within the last 5 years prior to enrolment.Conditions associated with an estimated life expectancy of under 2 years.Coronary calcium score >1000.

### Study groups

2.5

One thousand patients who meet the selection criteria will be included in the trial and will be divided into 2 groups, namely patients in whom screening CCTA analysis identifies only non-eccentric coronary plaque (group 1) and patients in whom CCTA analysis reveals the presence of at least 1 eccentric significant coronary plaque producing a significant luminal narrowing (group 2).

### Study procedures and outcome assessment

2.6

In all patients clinical data including sex, age, comorbidities, history of coronary artery disease, stroke, peripheral arterial disease, diabetes, smoking status, as well as clinical status and laboratory tests (creatinine, total cholesterol, low-density lipoprotein [LDL]-cholesterol, triglycerides) will be recorded. All patients will undergo CCTA scanning of the coronary arteries at screening and will be enrolled in the study if CCTA reveals the presence of at least 1 obstructive coronary plaque in any coronary artery. In randomized patients, CCTA scanning will be followed by complex image postprocessing for assessment of plaque composition, morphology, and geometry, using available research software for plaque reconstruction and analysis.

#### CCTA scanning protocol

2.6.1

CCTA will be performed with a 128-slices single source CT scanner with retrospective electrocardiographic gating, at a tube voltage of 100 kV, a gantry rotation time of 330 ms and a collimation of 128 × 0.6. Oral beta-blockers will be administered to all patients with a heart rate >65 beats/min in order to achieve the desired heart rate, and 0.4 mg nitroglycerin will be administered sublingually 2 minutes before scanning in order to obtain a coronary vasodilatation and thus a superior image quality. Contrast agent will be injected with a flow rate of 5 mL/s in the antecubital vein, using an18-gauge venous catheter placed in the right cubital fossa, with a total contrast quantity between 80 and 100 mL adapted to patient body weight. Contrast administration will be followed by a flush of 50 mL saline solution with the same flow rate. CT datasets will be retrospectively reconstructed with a slice thickness of 0.6 using a medium soft-tissue convolution kernel and the phase with the fewest motion artifacts and best image quality will be selected for image analysis and for atheromatous plaques assessment.

#### Plaque reconstruction and analysis

2.6.2

All reconstructed CCTA images will be further evaluated semi automatically using a three-dimensional (3D) contour detection algorithm (Syngo.via Multimodality Workplace, Siemens, Frontier–Coronary Plaque Analysis platform, Siemens, Erlangen, Germany). All coronary vessels with a diameter of at least 2 mm will be assessed using the 19 coronary segments model.

Quantitative evaluation of the atheromatous lesions will include plaque length, vessel volume, lumen volume, plaque volume, and the severity of luminal narrowing. The volumetric measurements will be performed using as reference the proximal and the distal extremities of the plaques, and assessment of plaque composition will include determination of dense calcium and non-calcified plaque components, such as lipid rich and fibrotic tissue.

Qualitative assessment of plaque characteristics will investigate the presence of vulnerability features inside the coronary plaque: PR, LAP, SC, and NRS.

#### Study definitions

2.6.3

In this study, a significant coronary plaque is defined as a plaque producing at least 50% luminal narrowing. The remodeling index (RI) represents the ratio between the cross-sectional area at the site of maximum stenosis divided by the average of the proximal and distal reference cross-sectional areas, and PR is defined as a remodeling index of 1.1 or greater.^[11]^ Plaques having at least 10% of their content non-calcified, with a CT density of <30 HU will be classified as LAP.^[12]^ SC are defined by a small dense area (>130 HU) surrounded by non-calcified plaque tissue.^[13]^ NRS will be considered present following identification of a non-calcified plaque with a central area of low attenuation in contact with the lumen, and a ring-like higher attenuation tissue, surrounding the central area.^[11,14]^

Cross-sectional plaque eccentricity will be assessed according to the location of the circulant lumen in a transverse section at the level of maximum stenosis. The cross-sectional eccentricity (CE) index will be calculated as follows: (maximum wall thickness – minimum wall thickness)/maximum wall thickness. Eccentric lesions will be defined as having a CE index of 0.3 or greater, whereas concentric lesions will be defined as having a CE index of <0.3. Longitudinal plaque eccentricity, defined as stenosis with an abrupt narrowing of the proximal or distal edge, will be assessed according to the location of maximum stenosis in a longitudinal section. The longitudinal eccentricity (LE) index will be calculated as the ratio of distance between the proximal end of the lesion and the place of maximum stenosis to the lesion length.^[15]^ Lesions with an LE index of ≤0.4 will be classified as descendent; lesions with an LE index of ≥0.6 will be classified as ascendant; and intermediate lesions with an LE index between 0.4 and 0.6 will be classified as non-eccentric plaques.

### Study time

2.7

The clinical trial will be conducted from November 2018 to August 2019, followed by a 24-months follow-up.

### Outcomes

2.8

The primary outcome of the study is represented by the rate of MACE during follow-up. Secondary outcome refers to coronary plaque vulnerability associated to plaque eccentricity, based on the number of vulnerability markers in eccentric versus concentric plaques.

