### Participation timeline

2.9

Screening (Day 0)

Obtain and document consent from participant on study consent form.Verify inclusion/exclusion criteria.Imaging: 128-multislice CT angiography scanning and basic plaque assessment—presence of coronary plaque and degree of luminal narrowing.

Baseline (day 0):

-Obtain demographic information, medical history, medication history, alcohol, and tobacco use history.-Record results of physical examinations and 12-lead ECG.-Collect blood specimens.-Imaging: image post-processing for complex plaque assessment—plaque morphology, composition, and geometry

Visit 1 (month 6):

-Record results of physical examinations, 12-lead ECG, and medical history.-MACE assessment.

Visit 2 (month 12):

-Record results of physical examinations, 12-lead ECG, and medical history.-MACE assessment.

Visit 3 (month 18):

-Record results of physical examinations, 12-lead ECG, and medical history.-MACE assessment.

Final study visit (month 24):

-Record results of physical examinations, 12-lead ECG, and medical history.-Repeat CCTA and plaque assessment.-End-point evaluation.

Figure 1 illustrates the GEOMETRY diagram with the flowchart that will be used in the study.

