### Sample size

2.10

The study will include 1000 subjects with suspected CAD who are referred to CCTA by the attending physician and in which presence of at least 1 coronary plaque is confirmed by CCTA. After analysis of coronary plaques eccentricity index, patients will be distributed in 2 groups according to the presence or absence of significant eccentric lesions in coronary arteries.

Sample size calculation was performed using the StatMate 2.0 software (GraphPad Software, San Diego, CA). For sample calculation, the proportion of event-free population was estimated at 90%. According to this calculation, a sample size of 500 patients in each subgroup has a 90% power to detect an increase in MACE-free rates proportion of 0.054, with a significance level (alpha) of 0.05 (two-tailed). Therefore, the total sample size was established at 1000 patients.

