### Statistical analysis

2.11

Statistical analysis will be performed using Graph Pad InStat 3.10 software (GraphPad Software, San Diego, CA) at the level of significance 5%. All data will be checked for normality. Continuous variables with normal distribution will be presented as mean ± standard deviation and will be compared using *t* test. Non-normally distributed variables will be analyzed using the Mann–Whitney *U* test. Categorical variables will be expressed in numbers and percentages and will be compared using the Fisher exact test.

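### The only listed test that fits two-year MACE is a comparison of proportions, which has no place for a patient lost event-free before month 24; a time-to-first-MACE analysis would

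*Protocol article*

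**What the plan says.** All references are to the protocol article.

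- **Outcome (section 2.8).** "The primary outcome of the study is represented by the rate of MACE during follow-up". Section 1.2 sets the horizon at two years and includes all-cause mortality in the composite.
- **Follow-up (sections 2.7 and 2.9).** Enrolment is "followed by a 24-months follow-up". MACE is assessed at months 6, 12 and 18, and the end-point evaluation is at month 24.
- **Analysis (section 2.11).** "Categorical variables will be expressed in numbers and percentages and will be compared using the Fisher exact test". For continuous data the section names the t test and the Mann–Whitney U test. It names no time-to-event method and does not mention MACE.
- **Sample size (section 2.10).** For planning, "the proportion of event-free population was estimated at 90" per cent. With 500 patients per group, the stated power is 90% for a difference of 0.054 in the MACE-free proportion, two-sided alpha 0.05. Twice 500 is carried straight to the total of 1000.

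**The concern.** MACE yes/no is a categorical variable, and the sample size is a comparison of two proportions. Read together, sections 2.10 and 2.11 point to a 2×2 table of group by 24-month MACE status.

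Such a table needs a status for every patient. A patient who has a MACE and is then lost has one. A patient last seen event-free at month 12 does not, and without imputation has to be left out or entered as event-free. Leaving the patient out discards a year of event-free observation; entering the patient as event-free understates risk.

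Two things are at stake. One is precision, because the stated power presumes that all 1000 patients have a known status. The other is bias. The groups are formed by a plaque feature and not by randomisation, so equal loss in both cannot be taken for granted, and unequal loss would create a difference where none exists.

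**Working it through.** **Inputs.** From section 2.10: MACE-free proportions 0.90 and 0.90 + 0.054 = 0.954, so risks of 0.10 and 0.046; 500 per group; two-sided alpha 0.05. The loss rates (5% to 20% over 24 months) are assumptions, since the article gives none.

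**1. The plan's own figure.** Power = Φ{[Δ√n − 1.96√(2p̄(1−p̄))] / √(p₁(1−p₁) + p₂(1−p₂))}, with Δ = 0.054 and p̄ = 0.073.

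- √(2 × 0.073 × 0.927) = 0.3679; √(0.0900 + 0.0439) = 0.3659.
- n = 500: (1.2075 − 0.7210)/0.3659 = 1.329, power **90.8%**. Exact power of the Fisher test by enumeration is 89.5%. The stated 90% is reproduced.

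**2. Power if every lost patient is dropped.**

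- 10% loss, n = 450: (1.1455 − 0.7210)/0.3659 = 1.160, power **87.7%**.
- 20% loss, n = 400: (1.0800 − 0.7210)/0.3659 = 0.981, power **83.7%**.

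This is the harshest version, because it also discards lost patients whose MACE had already been recorded. For gentler handling, take constant event and loss hazards over 24 months. The share with an observed event is then

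o = [ln(1−p) / (ln(1−p) + ln(1−L))] × [1 − (1−p)(1−L)],

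where p is the 24-month risk and L the loss.

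| Loss in both groups | Observed risks, lost counted event-free | Power | Risks if only those lost without an event are dropped | Power |
|---|---|---|---|---|
| 10% | 9.50% vs 4.37% | 89.3% | 10.50% vs 4.84% (n ≈ 452 and 451) | 89.3% |
| 20% | 8.98% vs 4.13% | 87.4% | 11.09% vs 5.13% (n ≈ 405 and 402) | 87.4% |

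The dropped-patient risks are o / [o + (1−p)(1−L)]. Counting lost patients as event-free shrinks the 5.4-point difference to 5.13 points at 10% loss and 4.85 at 20%.

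**3. Log-rank with censoring.** The hazard ratio is ln(0.90)/ln(0.954) = 2.24. Expected events are 500 × (0.10 + 0.046) = 73 with full follow-up, 500 × (0.0950 + 0.0437) ≈ 69 at 10% loss and 500 × (0.0898 + 0.0413) ≈ 66 at 20%.

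- Schoenfeld, Φ(½√E · ln HR − 1.96): 93.1%, 91.8% and 90.3%.
- Freedman, Φ(√E · (HR−1)/(HR+1) − 1.96): 90.4%, 88.9% and 87.2%.

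The choice of formula moves the result by 2 to 3 points. That is as much as the gap between the log-rank test and a 2×2 table that keeps observed events, so a power gain over such a table is not established.

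**4. Bias when loss differs.** Let the true risk be 10% in both groups, with loss of 5% in one and 20% in the other.

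- *Lost counted as event-free.* With loss uniform over follow-up and events accruing evenly, apparent risk = 0.10(1−L) + 0.05L: 0.095 + 0.0025 = **9.75%** and 0.080 + 0.010 = **9.0%**. The constant-hazard formula gives 9.75% and 8.98%.
- *Those lost without an event dropped.* 0.0975/(0.0975 + 0.90 × 0.95) = **10.2%** and 0.0898/(0.0898 + 0.90 × 0.80) = **11.1%**.

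The group with more loss looks safer by 0.75 points under one rule and riskier by about 0.85 under the other: 14% and 16% of the 5.4-point target, with opposite signs. Kaplan–Meier would estimate 10% in both groups, because loss in this example is unrelated to risk.

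**The case against.** The strongest reply is that a 24-month proportion is a legitimate target here. Every patient has the same planned follow-up, so there is no built-in administrative censoring. Death from any cause is a MACE component and therefore an event, not a loss. The planned comparison also matches the sample size. All of this stands: if follow-up is nearly complete, the comparison of proportions is valid, and the six-monthly visits are not a fault.

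A reader might infer that the plan assigns the Fisher test to MACE by name, or that it will drop lost patients or count them as event-free. The article says neither. The statement "will be compared using the Fisher exact test" refers to categorical variables in general. The link to MACE is an inference from that sentence, the absence of any other suitable test and the proportion-based sample size. Rules for lost patients may stand in a fuller document, and the article's silence on them is not itself the criticism.

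Nor should one say that every patient lost early lacks an outcome, since those with an earlier MACE have a known status. The loss rates, and above all 5% vs 20%, are illustrations; nothing in the article suggests so wide a gap at one centre with one visit schedule.

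What remains is that sections 2.10 and 2.11 do set out a method, and that method handles incomplete follow-up less well than one the visit schedule already supports.

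**Conclusion.** The point holds as a cheap improvement, not as an error that invalidates the plan. The stated power reproduces and the planned comparison is sound with nearly complete follow-up.

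Under assumed loss of 10% to 20%, the cost in power is at most 3 to 7 points (90.8% to 87.7% or 83.7%), and about 1.5 to 3.5 points if events seen before loss are kept. The better reason for change is bias. Under assumed loss of 5% vs 20%, a spurious difference of about 0.75 to 0.85 points appears, and its sign depends on how lost patients are handled. Censoring removes it only if loss is unrelated to risk; informative loss would bias a survival analysis too.

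**What to change.** In section 2.11, name the primary analysis: time from index CCTA to first MACE, censored at last contact or 24 months, whichever comes first. Report Kaplan–Meier 24-month MACE-free rates with 95% CIs by group and compare the groups by log-rank test or Cox model. The Kaplan–Meier rate estimates the same MACE-free proportion that section 2.10 plans on, so the target does not change. Use event and last-contact dates obtained at the scheduled visits, and state that censoring assumes non-informative loss.

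The cost is slightly more analysis work and software that supports survival analysis, which should be checked for the package named in section 2.11. No extra patients or visits are needed.

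### The secondary outcome compares plaques, but the only tests named assume independent observations although a patient may contribute several plaques

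*Protocol article*

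**What the plan says.** Section 2.8 (Outcomes) defines the secondary outcome as plaque vulnerability, "based on the number of vulnerability markers in eccentric versus concentric plaques". Section 2.6.3 (Study definitions) assigns the exposure lesion by lesion: "Eccentric lesions will be defined as having a CE index of 0.3 or greater", and concentric below that value. The markers are the four CCTA features in section 2.6.2 (positive remodeling, low-attenuation plaque, spotty calcification, napkin-ring sign), so a plaque can score 0 to 4.

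Three places bear on how many plaques a patient can supply:

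- Section 2.3 enrols patients "in whom CCTA will identify presence of at least 1 significant coronary plaque".
- Section 2.6.2 states that "All coronary vessels with a diameter of at least 2 mm will be assessed using the 19 coronary segments model".
- Section 2.5 places a patient in group 2 when "CCTA analysis reveals the presence of at least 1 eccentric significant coronary plaque".

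Section 2.11 (Statistical analysis) then lists the methods. "Continuous variables with normal distribution will be presented as mean ± standard deviation" and are compared by t test. "Non-normally distributed variables will be analyzed using the Mann–Whitney" U test. Categorical variables "will be compared using the Fisher exact test". It gives no per-patient summary, index-lesion rule or method for correlated observations.

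**The concern.** Plaques in one patient share that patient's risk factors, treatment, scan quality and contrast timing, so their marker counts are likely to be correlated. The three named tests treat each plaque as a separate, independent unit. If eccentricity also tends to run in the same patients, the standard error implied by these tests is too small and they reject too often. If the contrast is mainly within patients, the standard error is too large and the tests lose power.

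The association of eccentricity with vulnerability is part of the secondary objective (section 1.2), of the design statement (section 2.1) and of the hypothesis in the Discussion. It is one of the study's main claims, and its p-value would come from this comparison.

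**Working it through.** **The plan's own figure.** The only calculation in the article is for MACE: 500 per group, 0.90 versus 0.954 event-free, two-sided alpha 0.05.

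- Mean proportion 0.927; null SE = √(2 × 0.927 × 0.073 / 500) = 0.01645.
- Alternative SE = √((0.90 × 0.10 + 0.954 × 0.046) / 500) = 0.01636.
- z = (0.054 − 1.96 × 0.01645) / 0.01636 = 1.33, so power is 90.8%.

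The stated 90% is reproduced. It concerns patients and does not bear on the plaque comparison, for which no calculation is given.

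**Inputs for the plaque comparison.** The unit, the exposure and the tests come from the sections cited above. The number of plaques per patient (m), the within-patient correlation of the marker count (ICC_M) and that of eccentricity (ICC_E) are not in the document. All three are assumptions and are shown as ranges.

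**Formula.** For an exposure that varies between plaques, the variance is multiplied by

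DE = 1 + (m − 1) × ICC_M × ICC_E,

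and a test run at nominal 5% has real type I error 2 × [1 − Φ(1.96 / √DE)].

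| m | ICC_M | ICC_E | DE | 1.96/√DE | Real type I error | SE too small by |
|---|---|---|---|---|---|---|
| 1 | any | any | 1.00 | 1.96 | 5.0% | 0% |
| 2 | 0.3 | 0 | 1.00 | 1.96 | 5.0% | 0% |
| 2 | 0.3 | 0.5 | 1.15 | 1.83 | 6.8% | 7% |
| 2 | 0.3 | 1 | 1.30 | 1.72 | 8.6% | 12% |
| 3 | 0.3 | 0.5 | 1.30 | 1.72 | 8.6% | 12% |
| 3 | 0.3 | 1 | 1.60 | 1.55 | 12.1% | 21% |
| 3 | 0.5 | 1 | 2.00 | 1.39 | 16.6% | 29% |

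**Simulation.** 1000 patients, no true association, a 0–4 marker count, half of plaques eccentric, 1500 runs per setting.

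| m | ICC_M | ICC_E | t test | Mann-Whitney | Cluster-robust |
|---|---|---|---|---|---|
| 1 | 0.3 | 1 | 4.1% | 4.3% | 4.1% |
| 2 | 0.3 | 0 | 5.3% | 4.9% | 5.2% |
| 2 | 0.3 | 0.5 | 6.9% | 7.0% | 5.9% |
| 2 | 0.3 | 1 | 7.9% | 7.3% | 4.0% |
| 3 | 0.3 | 0.5 | 5.9% | 6.5% | 3.9% |
| 3 | 0.3 | 1 | 10.3% | 9.9% | 5.1% |
| 3 | 0.5 | 1 | 16.1% | 16.1% | 5.7% |

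Some simulated values lie below the formula. One reason is that the correlations were set on an underlying normal scale, before the count and the eccentric/concentric split were formed, which weakens them. For example, 0.5 on that scale becomes (2/π) × arcsin(0.5) = 0.33 for a half-and-half split. The Monte Carlo standard error near 7% is √(0.07 × 0.93 / 1500) = 0.7 percentage points.

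**Unequal numbers of plaques.** A second simulation (2000 runs) gave patients 1–4 plaques with probabilities 0.4, 0.3, 0.2 and 0.1 (mean 2.0). The size-weighted m is (0.4 × 1 + 0.3 × 4 + 0.2 × 9 + 0.1 × 16) / 2.0 = 2.5. With both correlations equal to 0.2, 0.4 or 0.6, DE = 1 + 1.5 × ICC² = 1.06, 1.24 and 1.54. The formula then gives 5.7%, 7.8% and 11.4%, against 6.1%, 7.1% and 10.6% simulated for Mann-Whitney.

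**The opposite direction.** If every patient supplies exactly one eccentric and one concentric plaque, ICC_E is −1. With ICC_M 0.3, DE = 1 − 0.3 = 0.70, 1.96/√0.70 = 2.34, and the type I error is 1.9%. The simulated t test gave 3.3%. Both are conservative.

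**The case against.** The strongest reply is that the weakness is conditional. The article never says how many plaques a patient contributes, and reading all vessels does not settle which lesions enter the analysis. Section 2.11 is a short, generic paragraph that ties no test to the secondary outcome, and an analysis plan that is not shown could define an index lesion or a clustered variance. Cross-sectional eccentricity is measured locally, at the point of maximum stenosis, so its within-patient correlation could be low and the inflation close to nil.

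Much of this stands. The size is not known, and the lower assumed settings give only 6–7%. For the simulated 6.1% above, the 95% Monte Carlo interval is about 5.1–7.1%. A reader might infer that the p-values are certainly wrong, or certainly too small. The document does not support that: the error can be nil or conservative. Nor does it support a claim about wrong error bars. Only mean ± SD is planned, and clustering distorts standard errors and intervals.

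The reply does not remove the point. The article does not leave the method open: it sets a plaque-level contrast and lists only independent-sample tests. Its grouping rule, at least one eccentric plaque versus only non-eccentric plaque, allows for several plaques of mixed type in one patient.

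**Conclusion.** The point holds in conditional form. Where patients contribute more than one plaque, the plaque-level p-values from the t, Mann-Whitney and Fisher exact tests, and any confidence intervals built the same way, are not valid because within-patient correlation is ignored.

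The assumed range runs from no error to about 7–12% at 2–3 plaques per patient with moderate marker correlation, and about 17% at the extreme setting. It drops below 5%, to about 2–3%, when the two plaque types are balanced within every patient. These figures rest on assumed plaques per patient and assumed correlations.

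A reader might extend the criticism to the main result. That would be mistaken: MACE is counted per patient, and neither that comparison nor its sample size is affected.

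**What to change.** In section 2.11, state that the unit of the secondary analysis is the plaque, and analyse the 0–4 marker count with patient as the cluster. Either a GEE with robust variance or a mixed model with a patient random intercept will do. Treat the presence of each single marker in the same way, since a plaque-level Fisher test has the same defect. Alternatively, pre-specify one plaque or one summary per patient, after which the named tests are adequate. Keep the t, Mann-Whitney and Fisher tests for patient-level variables. Report the number of plaques per patient, so that readers can judge how much clustering matters.

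The cost is a few sentences and slightly more analysis work, in software that fits such models. Intervals may widen. Using one plaque per patient is simpler but discards information. No new data are needed.

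### The plaque-level secondary comparison is unpaired and unadjusted, so patient differences can enter an estimate meant to describe the lesion; a within/between-patient model should be reported beside it

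*Protocol article*

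**What the plan says.** All references are to the protocol article.

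- **Outcome (2.8).** The secondary outcome is vulnerability associated with eccentricity, "based on the number of vulnerability markers in eccentric versus concentric plaques". The unit compared is the plaque.
- **Exposure (2.6.3).** Geometry is assigned lesion by lesion: "Eccentric lesions will be defined as having a CE index of 0.3 or greater", and concentric below that value.
- **Markers (2.6.2).** "Qualitative assessment of plaque characteristics will investigate the presence of vulnerability features inside the coronary plaque: PR, LAP, SC, and NRS". Each plaque therefore carries 0 to 4 markers.
- **Plaques per patient (2.6.2, 2.5).** "All coronary vessels with a diameter of at least 2 mm will be assessed using the 19 coronary segments model", so one patient can contribute several plaques. Group 2 requires only "at least 1 eccentric significant coronary plaque", so its patients may also carry concentric ones.
- **Tests (2.11).** A t test for normally distributed variables; otherwise "Non-normally distributed variables will be analyzed using the Mann–Whitney" U test. Categorical variables "will be compared using the Fisher exact test". All three are unpaired and unadjusted.
- **Covariates (2.6).** Age, sex, diabetes, smoking and lipids are recorded, but no stated analysis uses them.
- **Hypothesis (section 3).** Lesion geometry is held to affect the vulnerability of the plaque, through the stress acting on the atheroma.

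**The concern.** Sections 2.8 and 2.11 together set eccentric plaques against concentric plaques regardless of whose they are. To a large extent the two sets come from different people. Suppose some patient characteristic (diabetes, lipids, treatment, noise of that scan) makes plaques both more often eccentric and richer in markers. The comparison then shows a difference even if, within any one patient, eccentric and concentric plaques are alike.

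This is bias in the estimate. It is separate from the understated standard error that several plaques per patient cause, and repairing the standard error alone leaves it in place. What is at stake is interpretation: a positive result would be read as evidence for a plaque-level marker when it might describe only the kind of patient. The bias can go in either direction, depending on the signs of the two shifts.

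**Working it through.** **The plan's own figure.** The article gives no power or precision figure for this outcome. Its only calculation (2.10) is for MACE: 500 per group, 0.90 against 0.954, two-sided alpha 0.05. Null SE = √(2 × 0.927 × 0.073 / 500) = 0.01645; alternative SE = √((0.09 + 0.0439) / 500) = 0.01636; power = Φ((0.054 − 1.96 × 0.01645) / 0.01636) = Φ(1.33) = 0.908. This agrees with the stated 90% and has no bearing on the present point.

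**Assumed inputs, none from the article.** 1000 patients; plaques per patient 1 + Poisson, mean 1.5, 2 or 3; 50% or 80% of plaques eccentric; four markers, each present with log-odds −1 (probability p = 0.269). A standard-normal patient factor shifts the log-odds of eccentricity by *a* and of each marker by *b*. There is no plaque-level effect.

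- Very weak: a = 0.15, b = 0.10.
- Weak: a = 0.3, b = 0.2 (odds ratios per SD 1.35 and 1.22).
- Moderate: a = 0.5, b = 0.3 (1.65 and 1.35).

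**Spurious difference.** To first order the patient factor differs by *a* between the two plaque sets, so

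spurious difference ≈ 4 p(1 − p) · a · b = 4 × 0.269 × 0.731 × a × b = 0.787 a b.

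- Very weak: 0.787 × 0.015 = 0.012 markers.
- Weak: 0.787 × 0.06 = 0.047 (simulated about 0.04-0.05).
- Moderate: 0.787 × 0.15 = 0.118 (simulated 0.11-0.12).
- Either shift zero: 0.

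A genuine plaque effect of log-odds 0.15 gives 0.787 × 0.15 = 0.118, the same as the moderate factor. The planned test cannot tell the two apart.

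**False positives, hand check at a mean of 2 plaques, 50% eccentric (1000 plaques per set).** SE ≈ √(0.787 × 2/1000) = 0.0397.

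- Very weak: z = 0.012/0.0397 = 0.30, rejection about 6%.
- Weak: z = 1.19, about 22%.
- Moderate: z = 2.97, about 84%. This is slightly high, because the linear formula overstates larger shifts.

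**False positives by simulation, over 1.5 to 3 plaques and 50-80% eccentric.**

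| Shared patient factor | Pooled planned test | Within-patient contrast |
|---|---|---|
| Very weak | about 4-9% | near 5% |
| Weak | about 13-31% | near 5% |
| Moderate | about 48-90% | near 5% |

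When the factor moves geometry only, the pooled test rejected about 5-9%.

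**Patients carrying both plaque types.** With eccentric share π and mean extra plaques λ, and ignoring the patient factor, the proportion is 1 − π·exp(−(1 − π)λ) − (1 − π)·exp(−πλ).

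- π = 0.5, λ = 2: 1 − exp(−1) = 0.63.
- π = 0.5, λ = 1: 1 − exp(−0.5) = 0.39.
- π = 0.8, λ = 0.5: 1 − 0.724 − 0.134 = 0.14.

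**Cost in power.** True plaque effect log-odds 0.15, no patient factor, 50% eccentric:

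| Mean plaques per patient | Pooled | Within-patient |
|---|---|---|
| 3 | about 98% | about 89% |
| 2 | about 82% | about 59% |
| 1.5 | about 69% | about 32% |

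**The case against.** **No passage shows that such a factor exists.** The article offers no evidence of any patient characteristic acting on both the cross-sectional index and the marker count, and with half the weak shifts the pooled test is close to nominal. This stands, and it limits the point to a safeguard.

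**The pooled association is itself of interest.** Section 1.2 states the secondary objective as an association, and a CCTA marker is read across patients. This also stands, and it is why the pooled contrast should stay. It does not cover the lesion-level hypothesis of section 3, which the pooled contrast alone cannot support.

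**A short statistics paragraph in an article may leave modelling to a separate plan.** That is fair for details. Here, however, the article itself fixes the unit of comparison and names the tests, and all of them are unpaired. If an unseen plan already holds such a model, only the article's wording needs aligning.

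**A stronger reading is tempting:** that many patients will carry both plaque types, that the within-patient estimate costs little, and that it should therefore replace the pooled one as the basis of the conclusion. The article does not support this. Requiring at least one eccentric plaque allows mixed patients but does not show that they are common. Group 1 patients, who have only non-eccentric plaques, add nothing to the within-patient coefficient. The power loss is modest only at about 3 plaques per patient. Segment, stenosis degree and plaque volume also remain as confounders within a patient, so that coefficient is not free of bias either.

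**Conclusion.** The point holds as a low-cost improvement. Sections 2.8 and 2.11 leave the secondary comparison open to patient-level confounding while section 3 frames the question at the lesion. Whether the bias is trivial or large cannot be told from the article. The 13-31% and 48-90% false-positive rates rest on the assumed plaque numbers, eccentric share and shifts, and they fall to near nominal when the shared factor is very weak or acts on one side only. A reader might infer that a positive secondary result would be spurious. The article does not show that. It shows only that the planned analysis could not separate a lesion-level link from a difference between patients.

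**What to change.** In 2.8 and 2.11, keep the pooled contrast and add one plaque-level regression of marker count on:

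- (a) the plaque's eccentricity minus the patient's own mean eccentricity;
- (b) the patient's mean eccentricity;

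with patient-clustered standard errors. State which index defines eccentric here. Concentric is defined in 2.6.3 only through the cross-sectional index, while the longitudinal index has its own non-eccentric class.

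Report (a), (b) and the pooled estimate with confidence intervals, and the number of patients carrying both plaque types. Claim a lesion-level link only if (a) supports it; otherwise describe the result as an association that may reflect differences between patients.

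The cost is analysis work only, since geometry and markers are already scored per plaque at baseline. The downside is precision: (a) draws on perhaps 14-63% of patients under the assumptions above, so an inconclusive (a) must not be read as evidence of no link. It also leaves confounding by segment, stenosis degree and plaque volume, which should be acknowledged alongside the result.
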